#### 2.5.4. Parental Psychological Questionnaires

Sleep Disturbance Scale for Children (SDSC). The SDSC questionnaire [86] evaluates specific sleep disorders and provides an overall measure of sleep disturbances, suitable for use in clinical screens and research in populations aged 6 to 15 years. It consists of 26 items and examines 6 main categories that represent some of the most common sleep difficulties that affect children and adolescents: disorders of initiating and maintaining sleep, sleep breathing disorders, disorders of arousal/nightmares, sleep-wake transition disorders, disorders of excessive somnolence, and sleep hyperhidrosis (night-time sweating).

Parents are asked to read each item (e.g., “the child has difficulty falling asleep”) and indicate how frequently certain behaviors are exhibited by their children on a Likert scale from 1 (“never”) to 5 (“always”). Parents are also required to provide estimates of sleep quantity and time of onset in their children. For all categories, the raw scores are converted into t-scores. Lower scores reflect better outcomes and will be considered as an improvement.

Parent Stress Index (PSI), Italian adaptation. This questionnaire is the most widely used survey for assessing parental stress in clinical and research settings. The Italian adaptation of the PSI [87] is composed of 36 items and examines 3 main areas: parental distress, parent-child dysfunctional interaction, and difficult child. Parents are asked to read each item (e.g., “I often have the feeling of not being able to cope very well with situations”) and indicate their level of agreement on a Likert scale from 1 (“strong agreement”) to 5 (“strong disagreement”). For all areas, the raw scores are converted into z-scores. Higher scores signify better outcomes and will be considered as an improvement.

Transverse Symptoms Assessment Scale. This questionnaire is part of the Kiddie-SADS present and lifetime versions per the Diagnostic and Statistical Manual of Mental Disorders 5 [88]. It comprises 25 items and evaluates health and the relevant symptoms that are related to psychiatric disorders (depression, anger, irritability, mania, anxiety, somatic symptoms, carelessness, suicidal ideation/suicide attempt, psychosis, alterations in sleep, repetitive thoughts and behaviors, and substance use), yielding a comprehensive clinical picture of youth aged 6 to 17 years.

Parents are asked to read each item (e.g., “Did he/she look angry or lose his temper?”) and indicate how much or how often the child has exhibited specific symptoms in the last two weeks on a five-point Likert scale from 0 (“Absent or not at all”) to 4 (“Severe or almost every day”). Items that are related to suicidal ideation, suicide attempts, and use of substances are answered “Yes”, “No”, or “I don’t know”. Consistently high scores in a particular domain might indicate significant and problematic symptoms for the participant, which could justify further evaluation, treatment, and follow-up.

#### 2.5.5. Electrophysiological Measures (EEG)

EEG data will be collected at T0 (immediately before the first session of the interventions), T1 (immediately after the last session), T2, and T3 (before administration of the arithmetic, neuropsychological, and psychological measures). The data will be collected via Geltrode electrodes using a Starstim device (8 channels: AF7, AF8, F3, F4, P3, P4, P7, P8 sites, Neuroelectrics) at a sampling rate of 500 Hz for 5 min in the resting state with eyes closed.

The Geltrode is a wet EEG electrode that provides a rear-fill aperture for the gel supply. It requires a conductive electrode gel and can be used in scalp areas with or without hair. The Geltrode has an Ag/AgCl-coated core that is 12 mm in diameter. It has a rear-fill aperture, and the contact area is approximately 1 cm^2^. The Geltrode electrode in the desired position of the wireless cap will be inserted. After the cap is placed on the head of the participant, a curved syringe will be used to inject the conductive gel through the hole on top of the electrode. Impedance will be kept below 10 kΩ. We will use EEG data in an exploratory manner to detect differences in spectral power frequencies. The EEG will serve as a noninvasive, objective biomarker for tRNS-induced effects and will be considered to be a correlate of behavioral improvements.

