### 2.3. Design, Randomization, and Blinding

The study will use a between-subject, randomized, double-blind, and sham-controlled design.

The screen for clinical eligibility will be completed on Day 0 of the trial, before the stratified randomization. Randomization occurs immediately after a participant completes the screening assessment, ensuring concealment of allocation. Participants will be allocated randomly to the following conditions: (1) Frontal Group (active tRNS over bilateral dlPFCs + cognitive training); (2) Parietal Group (active tRNS over bilateral PPCs + cognitive training); and (3) Sham Group (Sham tRNS over bilateral dlPFCs/PPCs + cognitive training). An independent researcher will perform the stratified randomization. The stratified randomization will use the minimal sufficient balancing method to prevent imbalances in baseline and will be based on the participants’ demographics (e.g., age, IQ, gender) and MTq [70].

The investigators who assess the participants will be blinded to the allocation, as will the participants and their parents. An independent researcher will maintain the randomization information until the data collection is completed. An emergency code break envelope will be provided to the principal investigator and will only be opened in the case of an emergency, such as a serious adverse event that requires knowledge of the interventions to manage the participant’s condition.

A baseline assessment (see Figure 1) will be completed on Day 1 (T0), before the interventions are administered. Participants will undergo combined interventions for 10 days (5 consecutive days per week for 2 consecutive weeks: from Day 1 to Day 5 and from Day 8 to Day 12). To minimize the influence of intracircadian variations, participants will attend stimulation sessions each day at the same time. Participants will also complete an assessment at the end of the interventions (Day 12, T1), 1 week later (Day 19, T2), and 3 months later (Day 102, T3). At the last follow-up, after the assessment, participants will be asked to guess their stimulation condition by the principal investigator.

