### 2.5. Outcome Measures

As described, the outcome measures will be presented to each participant individually at T0, T1, and each follow-up (T2 and T3) in a quiet room in random order to control for the effects of fatigue. The outcome measures will include arithmetic, neuropsychological, self-administered, and parental psychological questionnaires and electrophysiological measures.

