## 3. Data Analysis

### 3.1. EEG Preprocessing

EEG preprocessing will be performed separately for data that are collected before (T0) and after the interventions (T1, T2, T3), with the examiner being blinded to the stimulation conditions for all preprocessing steps. First, the EEG file will be imported into MATLAB (R2020b, The Mathworks) using the EEGlab toolbox (eeglab2021.0) [92], and channels will be located on the scalp model using the NE_EEGLAB_NIC_Plugin_v1.9 plugin (Neuroelectrics). Data will be band-pass-filtered from 1 Hz (high-pass) to 70 Hz (low-pass). The line noise (~50 Hz) will be removed. Next, the data will be divided into windows of 1 sec (epochs), and EEG epochs with muscle, electrode, and blinking artifacts will be manually removed. Independent component analysis will be conducted, and any period of nonindependence between components will be identified by eye. The spectral power for each epoch in four frequency bands [theta (θ) = 4–7.99 Hz; alfa (α) = 8–12.99 Hz; beta (β) = 13–29.99 Hz; gamma (γ) = 30–50 Hz] will be computed and averaged across epochs for each participant.

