### 3.2. Statistical Analysis

The Shapiro–Wilk test will be used to test the normality of the data, and Levene’s test will be performed to analyze the homogeneity of the variances. When the data are normally distributed and the assumption of homogeneity is not violated, parametric analyses will be computed. When one assumption is not met, nonparametric tests will be conducted or log-transformation of the distribution will be applied, if appropriate. When appropriate, sphericity will be verified by Mauchly’s sphericity test. When sphericity is not met, Greenhouse–Geisser correction will be applied.

Chi-square analysis will be used to compare groups with regard to demographics, blindness, and safety measures (categorical variables).

Linear mixed-effects models, which account for within-subject correlations more optimally than analysis of variance and automatically handle missing values, allowing maximum use of available data [93], will be run to compare groups for primary (continuous variables: number line subtest) and secondary outcomes (continuous variables: arithmetic, neuropsychological, and psychological measures). The R package lme4 v1.1–17 [94,95], which estimates model parameters using restricted maximum likelihood estimation and computed *p*-values per Satterthwaite’s method [96], will be used. The linear mixed-effects models will include Group (Frontal, Parietal, and Sham) and Time (T0, T1, T2, T3) as fixed factors and Participants as the random factor. Baseline performance will be included as a covariate in our model, because it allows us to make better adjustments for minor differences in pretreatment means. The same analysis will be performed for the training accuracy data, including Group (Frontal, Parietal, and Sham) and Day (from 1 to 10) as fixed factors and participants as the random factor.

Pearson’s correlation will be used to determine whether and the extent to which arithmetic improvements are related to changes in neuropsychological measures, psychological measures, and spectral power of EEG frequency bands at T1, T2, and T3 (from T0).

The statistical results will be corrected for multiple comparisons by Bonferroni’s correction where appropriate.

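### The resting EEG is recorded at a different point of the visit at T0, T1 and T2/T3, and T0 files are processed apart from later files, so the exploratory change-from-T0 correlations can be weakened or distorted.

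*Protocol article*

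**What the plan says.** Section 2.5.5 fixes the EEG at the start and end of treatment relative to the stimulation sessions: "EEG data will be collected at T0 (immediately before the first session of the interventions), T1 (immediately after the last session". At the two follow-ups it fixes the EEG relative to the tests: "T2, and T3 (before administration of the arithmetic, neuropsychological, and psychological measures". It does not say where the T0 recording falls relative to the tests.

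Section 2.3 puts the baseline battery on the same day as session 1: "A baseline assessment (see Figure 1) will be completed on Day 1 (T0), before the interventions are administered". Section 2.5 says that the outcome measures, among which it counts the electrophysiological ones, are presented at every visit "in a quiet room in random order to control for the effects of fatigue".

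On processing, section 3.1 states: "EEG preprocessing will be performed separately for data that are collected before (T0) and after the interventions (T1, T2, T3". Artefact epochs are removed manually, components are judged by eye, and the examiner is blinded to stimulation condition; time point is not mentioned.

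On analysis, section 3.2 uses EEG only in Pearson correlations of arithmetic improvement with change in "spectral power of EEG frequency bands at T1, T2, and T3 (from T0". The mixed models cover the arithmetic, neuropsychological and psychological measures. Section 3.3, item 4, places the EEG hypothesis within the Frontal and Parietal groups, at least at T1. Section 2.5.5 calls the EEG use exploratory, but also a biomarker of tRNS-induced effects.

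**The concern.** A change score is interpretable when both recordings are made in comparable states. Here the reference recording and the later ones differ by design. T1 follows 20 minutes of stimulation with training. T2 and T3 precede testing. T0 precedes a session and, as far as one can tell, follows testing. Resting spectral power may depend on how tired the child is, and the protocol itself treats fatigue as real: section 2.5 randomises test order because of it, and section 2.7 lists fatiguing tasks as a risk.

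The separate handling of T0 files adds a second difference along the same axis. If the by-eye rejection standard drifts between the two batches, the drift enters every change score.

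At stake is the fourth research objective in section 1.3, the link between EEG change and arithmetic improvement, and the use of EEG as a marker of treatment responders proposed in section 4.

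**Working it through.** **Step 1. Order of procedures at each visit.**

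| Visit | Day | EEG position (2.5.5) | Tests relative to EEG |
|---|---|---|---|
| T0 | 1 | immediately before session 1 | not stated; 2.3 completes the battery before the interventions |
| T1 | 12 | immediately after the last session | not stated |
| T2 | 19 | before the tests | after |
| T3 | 102 | before the tests | after |

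If the EEG comes immediately before session 1 and the battery is also complete before session 1, the battery does not fit between them and so comes first. This is an inference from two sections. Section 2.5 points elsewhere: with EEG inside a random order, its position at T0 would vary from child to child, and the fixed positions in 2.5.5 could not hold. On either reading, T0 is not consistently matched to T2 and T3. Section 2.3 refers to Figure 1 for the baseline assessment; the figure was not available for this review and may show the order.

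**Step 2. What a state component does to the planned statistic.** Let A be arithmetic gain and D the EEG change free of state effects, both with SD 1 and true correlation ρ. The observed change is D + μ + S, where μ is a shift common to all children and S varies between children with SD s (in units of the SD of EEG change) and correlates c with A. S is taken to be related to D only through A. Then

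r = (ρ + s·c) / √(1 + s² + 2·ρ·s·c).

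μ does not appear, so a uniform shift has no effect on r. The schedule is the same in all arms and sham receives the same training and procedures (2.4.2), so μ also cancels in active minus sham.

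**Step 3. Numbers.** The documents give none for s or c, so all are assumed. Simulated means (26 per arm, the per-group number before dropout in 2.6; 10,000 replicates; μ = 0.5 in every row below the first) are in brackets.

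| s | c | r if ρ = 0 | r if ρ = 0.30 |
|---|---|---|---|
| 0 | – | 0 (0.00) | 0.300 (0.294; 0.295 with μ = 0.5) |
| 0.3 | 0 | 0 (0.00) | 0.30/√1.09 = 0.287 (0.280) |
| 0.5 | 0 | 0 (0.00) | 0.30/√1.25 = 0.268 (0.265) |
| 0.3 | 0.5 | 0.15/√1.09 = 0.144 (0.141) | 0.45/√1.18 = 0.414 (0.408) |
| 0.5 | 0.5 | 0.25/√1.25 = 0.224 (0.219) | 0.55/√1.40 = 0.465 (0.459) |

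In the simulation, μ = 0.5 moved the within-arm mean change by 0.50 SD and the active-minus-sham difference by about 0.00. The sign of c is unknown. By the same formula, c = −0.5 with s = 0.5 turns ρ = 0.30 into 0.05/√1.10 = 0.048.

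**Step 4. The same attenuation on another scale.** Let the fatigue SD x be expressed in units of the between-child SD of log power, and let the test–retest correlation be R. The variance of change is 2(1 − R), and with c = 0 the shrinkage factor is √[2(1 − R) / (2(1 − R) + x²)].

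- R = 0.8, x = 0.2: √(0.40/0.44) = 0.953
- R = 0.8, x = 0.5: √(0.40/0.65) = 0.784
- R = 0.9, x = 0.2: √(0.20/0.24) = 0.913
- R = 0.9, x = 0.5: √(0.20/0.45) = 0.667

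A true r of 0.50 would become 0.48 at the mildest of these and 0.33 at the worst. The worst case needs a fatigue variance of 0.25 against an ordinary retest-change variance of 0.20, which is extreme.

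**The case against.** The strongest reply is that the plan never states that T0 EEG follows the battery. A reader might infer that every child's reference recording is made when tired and every follow-up recording when rested. The documents do not establish this: the order is deduced, section 2.5 conflicts with it, section 2.7 allows breaks at any time, and Figure 1 may show something else. This stands. What is left is a conflict between sections and a stated lack of matching across visits.

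A reader might also infer that a mean shift in band power would be taken for a stimulation effect. Section 3.2 plans no within-arm test of mean EEG change, a uniform shift leaves Pearson's r alone, and it cancels against sham. This stands too. It does not remove the concern, because the only EEG analysis specified is the correlation of change scores, hypothesised within the active groups, and a component that differs between children does alter that.

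A third reply is that unmasked time point and clock hour at follow-up are details an article may leave out. For clock hour this is right, and it is not pressed. For preprocessing, separate handling of T0 files is stated, not omitted. But nothing says that the rejection criteria differ between batches; drift is a possibility only.

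Finally, moving the T0 recording does not help T1, the time point that section 3.3 names for the EEG hypothesis, and could widen the T0–T1 difference in state. This is correct and limits what the change can achieve.

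**Conclusion.** The point holds in a limited form. The EEG is recorded at non-matching points of the visit, sections 2.3, 2.5 and 2.5.5 do not agree on where the T0 recording falls, and T0 files are handled apart from later files with only condition masked. The exploratory correlations of arithmetic gain with EEG change from T0 can therefore be attenuated or distorted.

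The size is not known from the documents. If the state component is unrelated to arithmetic gain, the loss is slight at s of 0.3 to 0.5; factors as low as 0.67 require extreme inputs. Distortion matters more and requires a link between the state component and arithmetic gain, for which the documents give no evidence either way. At T1 there is an additional component: section 4 cites tRNS after-effects of up to 60 minutes, so that recording may reflect an acute effect as well as a lasting one.

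The primary outcome, the sample size and the group comparisons in section 3.2 are untouched. Severity is minor.

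**What to change.** In section 2.5.5, state that at T0 the EEG is recorded before any test, as at T2 and T3. In section 2.5, exempt EEG from the random order, and align section 2.3 and Figure 1 with this.

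In sections 2.5.5 and 3.2, describe the T1 recording as an immediate post-session measure and interpret its change from T0 as such, separately from T2 and T3.

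In section 3.1, process all of a child's files together under coded names and in random order, with time point masked as well as condition.

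The cost is a small reordering of the Day 1 visit and the recoding of file names; no procedure is added. The T0–T1 difference in state remains and should be acknowledged when the T1 correlations are reported.

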#### 2.5.6. Safety and Tolerability

Symptoms and side effects will be assessed using a standard questionnaire [89] to be completed by participants after each session and at each follow-up (T1, T2, and T3). The questionnaire lists adverse effects, such as headache, neck pain, scalp pain, tingling, itching, burning sensation, skin redness, sleepiness, trouble concentrating, and acute mood change. Participants will quantify the intensity of the symptoms or side effects that are related to tRNS as follows: (1) absent; (2) mild; (3) moderate; and (4) severe.

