### 2.7. Safety Considerations

There are minimal risks that are associated with participation in the study. The potential risks are as follows: (1)Transcranial random noise stimulation. Considering the paucity of safety data on tRNS, this technique is considered safe, as supported by a recent study in juvenile mice [61]. Previous studies [90,91] have shown that tRNS with the current intensity that we use here is less likely to be perceivable. Compared with tDCS, tRNS has the advantage of having higher cutaneous perception thresholds and lower response rates [90]. Adverse effects will be registered throughout the study. The experimenter will also follow participants for adverse effects after the end of the study.(2)Cognitive training/assessment. There is a risk that participants will find the tasks to be challenging, fatiguing, or boring. Should this occur, participants can take a break at any time or can discontinue the testing. Research staff will explain what to do and how to perform the tasks during study visits.

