### 2.8. Protection of Risks

To minimize any risk that is associated with tRNS, participants will be monitored throughout the stimulation sessions and asked to report any discomfort. If the scalp sensation is uncomfortable, the stimulation will be stopped. In the event of a headache, the stimulation will be stopped. All tRNS sessions will be administered and supervised continuously by a trained experimenter. There are no reports of seizures having been induced by tRNS in human participants. However, to avoid any chance of seizure, a prior history of neurological disorders is an exclusionary criterion for our study, and no participants will have a history of seizure. The risks that are associated with cognitive training and assessment are minimal. Nevertheless, breaks will be offered if participants experience frustration with the tasks.

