Although tDCS is the most widely used neuromodulatory technique during developmental ages [101,102], in the last few years tRNS popularity has sharply increased. While tRNS appears to have at least the same potential long-term effects as anodal tDCS [62], it is easier to blind than tDCS, making it preferable for double-blind studies [90,100]. Of importance, a number of studies showed that tRNS would induce more pronounced and consistent enhancements compared to tDCS in perceptual [91] and cognitive domains [103], as well as in clinical populations [73].

The selection of tRNS parameters was based (1) on a single study using tRNS in children with MLD [66] and (2) on evidence of the beneficial and safe effects of high-frequency tRNS in the motor [104,105], sensory-perceptual [60,106,107], and cognitive [108,109,110] domains and, specifically, in arithmetic tasks [62,65,66]. Regarding the current intensity, 1 mA is well tolerated in adults, without adverse effects [62,63,64,65,72], but guidelines for children recommend applying at least half of that for adults [111]. The decision to apply 75% of 1 mA was made after considering the parameters that influence the current distribution and density at the site of stimulation, such as a thinner scalp, less cerebrospinal fluid, and the smaller head size of the pediatric population [111,112,113].

Regarding the frequency band, tRNS can encompass a full-frequency range (typically from 0.1–640 Hz) or can be delivered at low or high frequency (by convention, respectively, from 0.1–100 Hz and 101–640 Hz) [58]. In our study, we decided to apply a high-frequency band of stimulation, given that only higher frequencies (100–500 Hz) of tRNS generate consistent excitability that lasts for up to 60 min after stimulation [58].

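### The side-effect form has no pre-stimulation rating and asks children to grade symptoms related to tRNS, so a pre-existing symptom cannot be told from a new one within a child

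*Protocol article*

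**What the plan says.** Section 2.5.6 (Safety and Tolerability) describes a standard questionnaire "to be completed by participants after each session and at each follow-up (T1, T2, and T3". It lists "headache, neck pain, scalp pain, tingling, itching, burning sensation, skin redness, sleepiness, trouble concentrating, and acute mood change". The rating instruction reads: "Participants will quantify the intensity of the symptoms or side effects that are related to tRNS as follows", with four grades from absent to severe.

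Other sections bear on the same point:
- Section 2.3: "Participants will also complete an assessment at the end of the interventions (Day 12, T1), 1 week later (Day 19, T2), and 3 months later", the last falling on Day 102.
- Section 2.4.2: the sham group goes through the same procedures as the active groups.
- Section 2.5: the outcome measures, which include the parent-rated sleep and symptom scales, are taken at T0, T1, T2 and T3.
- Section 2.7: "Adverse effects will be registered throughout the study", and "The experimenter will also follow participants for adverse effects after the end of the study".
- Section 2.8: "participants will be monitored throughout the stimulation sessions and asked to report any discomfort".
- Section 3.2: safety measures are compared between groups by chi-square.
- Section 3.3: the groups are expected not to differ on safety measures.

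**The concern.** The article fixes when the form is given, and neither T0 nor the start of a session is among those times. The arithmetic, neuropsychological, psychological and EEG measures all have a T0 value. The side-effect form, as described, does not.

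This matters because much of the symptom list is non-specific. Headache, neck pain, sleepiness, trouble concentrating and mood change can all be present when a child arrives, or can follow 20 minutes of training that Section 2.7 itself says may be fatiguing. Without a rating beforehand, nobody can say for a given child whether a symptom emerged with stimulation.

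The rating instruction adds a second problem. Read literally, it asks a blinded child, from 8 years 6 months, to decide what tRNS caused before grading it. Reports may then depend on which condition the child believes he or she is in.

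Safety over 10 sessions is the first research objective in Section 1.3, and the expected finding is no difference between groups. Imprecise symptom data make a non-significant result easier to obtain, and such a result could be read as reassurance.

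**Working it through.** The article states no figure on this point, so there is none to reproduce. The check is a reading of the schedule plus two illustrations under assumed rates.

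**Schedule.** The stated times for the form are after each of 10 sessions, T1 (Day 12), T2 (Day 19) and T3 (Day 102). Every one of these follows at least one stimulation.

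**Illustration 1: reports with no tRNS effect.** Assume a background probability *b* that a child has a given symptom after a session, independent across sessions. The chance of at least one report in 10 sessions is 1 − (1 − *b*)^10:

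| Assumed *b* per session | At least one report in 10 sessions |
|---|---|
| 5% | 40% |
| 10% | 65% |
| 20% | 89% |
| 30% | 97% |

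Independence is a simplification. Symptoms that cluster in the same children would lower these figures. The message is only that a single report says little about emergence.

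**Illustration 2: the arm comparison is not shifted by background.** Assume background headache of 10% in all arms and a true added 10 points under active stimulation. Without a baseline the form shows 20% v 10%. Counting only new or worsened symptoms, and if all the background is already present beforehand, it shows about 10% v near 0%. The difference is 10 points both ways.

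**What background does cost is precision.** Inputs: 34 per arm (Section 2.6), two-sided alpha 0.05 (assumed for this comparison), and a true excess of 20 or 30 points (assumed). Here *b* is the sham-arm proportion on whatever binary measure is compared. With p1 = *b*, p2 = *b* + excess and pbar their mean:

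- SE1 = √[(p1(1 − p1) + p2(1 − p2))/34]
- SE0 = √[pbar(1 − pbar) × 2/34]
- power = Φ[(p2 − p1 − 1.96 × SE0)/SE1]

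Worked line for *b* = 10% and excess 20 points: SE0 = √(0.20 × 0.80 × 2/34) = 0.0970; SE1 = √[(0.09 + 0.21)/34] = 0.0939; power = Φ[(0.20 − 0.1901)/0.0939] = Φ(0.105) = 54%.

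| Assumed *b* | SE1 of the difference (20-point excess) | Power, 20-point excess | Power, 30-point excess |
|---|---|---|---|
| 5% | 8.3 points | 64% | 89% |
| 10% | 9.4 points | 54% | 83% |
| 20% | 10.8 points | 43% | 75% |
| 30% | 11.6 points | 39% | 71% |

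A pre-stimulation rating moves the comparison up this table to the extent that the background is already there on arrival. Symptoms brought on by the training itself stay in all arms, so the gain is partial. These powers use the number recruited, so dropout would lower them.

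**The case against.** The strongest reply is that the trial has other safeguards, and most of that reply stands.

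*Delayed effects.* A reader might infer that asking after stimulation means later effects are missed. The documents do not support that. The form is repeated one week and three months after treatment. Section 2.7 promises registration throughout the study and follow-up beyond it. Parent-rated sleep and symptom scales run from T0 to T3. The Discussion's statement that high frequencies "generate consistent excitability that lasts for up to 60 min after stimulation" concerns cortical excitability and justifies the frequency band. It gives no time course for side effects. Any estimate of how little calendar time the form covers would need a recall window that the article does not state.

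*Bias from background.* A reader might also infer that ordinary symptoms bias the arm comparison. They do not: the sham arm has the same procedures, and illustration 2 leaves the difference unchanged. What remains is the loss of precision and of attribution within a child.

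*Wording.* Section 2.5.6 opens by saying that symptoms and side effects are assessed, so the phrase about tRNS may be loose drafting, not a scoring rule. It is therefore not established that unattributed symptoms are scored absent, or that children who guess sham under-report. Blinding limits the risk, and Section 4 describes tRNS as easier to blind than tDCS. Still, the restriction sits in the rating instruction itself, and a sham arm does not correct reports that follow perceived allocation.

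*Partial baseline.* The parent scales give a T0 value for sleep, mood and somatic symptoms. They use a different rater and scale, and the symptom scale looks back two weeks, so they cannot serve as the reference for a per-session form.

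*Unseen material.* The Figure 1 legend names the safety questionnaire, but the image is not shown and the full protocol is not at hand. A T0 form may be scheduled there.

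**Conclusion.** The point holds in a limited form. As Section 2.5.6 is written, there is no pre-stimulation rating, so an existing symptom cannot be told from a new one within a child. The grading instruction also invites a blinded child to judge cause, which may filter reports by perceived allocation. The size of that filter cannot be estimated from the article.

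The group-level comparison with sham remains valid but loses precision. In the illustration, power for a 20-point excess runs from 64% down to 39% as background rises from 5% to 30%. The background rates, the excess and the alpha are assumptions. Only the 34 per arm comes from the article.

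This is an inexpensive improvement to the safety data and not a flaw that invalidates the safety comparison.

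**What to change.** 1. Give the same questionnaire at T0 before the first stimulation, and a brief version before each later session. Keep the existing forms after each session and at T1, T2 and T3.
2. Record the intensity of every listed symptom whatever its supposed cause. Ask about relatedness to tRNS as a separate item.
3. Compare arms on symptoms that are new or worse than the pre-stimulation rating, and say which rating is the reference. Use the same-day rating for within-session change and the T0 rating for the whole course and follow-up. Otherwise a symptom that starts after one session and is still present the next day would drop out as pre-existing.
4. If Figure 1 or the full protocol already schedules a T0 form, correct Section 2.5.6 to match.

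The cost is a few minutes per visit at visits the child already attends, a wording change, and higher raw symptom counts in all arms. Stimulation and clinical management are not affected.
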